# Virtual Life Story Club Intervention to Improve Loneliness and Apathy in Community-Dwelling Older Adults: Protocol for a Mixed Methods Feasibility Study

**DOI:** 10.2196/70518

**Published:** 2025-06-04

**Keywords:** apathy, cognition, community-dwelling, loneliness, reminiscence therapy

## Abstract

**Background:**

Reminiscence therapy is a noninvasive, nonpharmacological intervention that has been shown to improve cognition, mood, functional status, quality of life, and apathy in older adults. Group reminiscence therapy combines structured social engagement and recounting of personal stories that address both social connection (a risk factor for cognitive decline) and cognition. Life Story Club is an established, nonprofit organization that provides virtual group reminiscence therapy for older adults to reduce loneliness and promote a sense of belonging and has not been formally studied.

**Objective:**

This study aims to explore the feasibility of a Life Story Club intervention to improve loneliness and apathy in community-dwelling older adults.

**Methods:**

A prospective, single-arm, single-center, pilot study will be conducted to compare loneliness and apathy in 50 lonely individuals without dementia at baseline who receive a virtual group reminiscence therapy intervention. The intervention will be delivered weekly over 12 weeks. Loneliness will be assessed with the UCLA Loneliness Scale and apathy will be assessed with the Apathy Evaluation Scale before and after the intervention. Feasibility will be assessed using quantitative and qualitative measures including feasibility of screening and enrollment, acceptability, and program satisfaction. Qualitative interviews will be conducted with a subset of 30 individuals to explore acceptability, barriers, and facilitators of the intervention.

**Results:**

The proposed study is funded by a pilot grant from the Institute for Clinical and Translational Research at Albert Einstein College of Medicine. Recruitment and data collection are planned for July 2025.

**Conclusions:**

This study will provide evidence for the feasibility of virtual group reminiscence therapy for community-dwelling older adults to reduce loneliness and apathy. Our approach is both innovative and pragmatic because we will leverage an existing community-based service, with an established infrastructure and track record within the community to deliver the intervention. As such, the proposed research has the potential for broad implications for community-based research and aligns with multiple translational science principles.

**International Registered Report Identifier (IRRID):**

PRR1-10.2196/70518

## Introduction

### Background

An estimated 6.9 million US older adults are living with Alzheimer disease and related dementias (ADRD) and the incidence increases with age [1]. ADRD is characterized by a progressive loss of cognition and function that eventually results in loss of independence and mortality. Currently, there are no curative treatments for ADRD. Thus, there is increased focus on nonpharmacological interventions that target modifiable risk factors for cognitive decline and dementia in older adults.

Apathy is a psychological syndrome characterized by a lack of motivation and interest, flattening of affect, and social withdrawal that predicts cognitive decline and increases the risk of ADRD by 20%-70% [2-10]. The prevalence of apathy ranges between 20% and 30% in community-dwelling older adults [11]. Apathy predicts the incidence of predementia syndromes mild cognitive impairment (MCI) and motoric cognitive risk syndrome, which is characterized by subjective cognitive complaints and slow gait [12,13]. Apathy is associated with social isolation related to a lack of interest in engagement [14]. Similarly, loneliness is highly prevalent in community-dwelling older adults (up to 43% [15]) and is associated with an increased risk of cognitive decline and ADRD [16,17]. Apathy and loneliness both represent potentially modifiable risk factors for cognitive decline and dementia and reminiscence therapy (RT) has been studied to target both these risk factors [18-20].

RT is a noninvasive, nonpharmacological intervention that has been shown to improve cognition, mood, functional status, quality of life, and apathy in older adults [18-24]. RT uses life story recollection in individual or group settings to improve psychological well-being. Prompts, photos, or music are all techniques used to trigger reminiscence, and the intervention can be delivered in person or virtually. Mechanisms for RT for apathy work through structured socialization with prompting from facilitators that stimulate motivation to engage. In addition, social stimuli lead to positive emotions through the sharing of personal stories. Sharing personal stories and a structured social environment that provides opportunities for meaningful engagement that may not happen in a casual social context address loneliness as well. A conceptual model of RT to address loneliness and apathy and how reminiscence may work as an intervention is visually depicted in Figure 1.

**Figure 1 figure1:**
[figure not shown]
Conceptual model of a reminiscence therapy intervention for loneliness and apathy and mechanisms for how the intervention may work. The left side of the figure represents the current proposal where we propose to investigate the feasibility of reminiscence therapy for loneliness and apathy. This research will inform and support a future randomized controlled trial of a reminiscence therapy intervention to improve cognition.

Cognitive decline in aging is multifactorial with multiple possible causes and there is significant variability in cognition based on the presence or absence of risk factors such as social factors (eg, loneliness) and apathy. In addition, the multiple aspects of social relationships (eg, meaning and purpose in life and social support) and psychological well-being (eg, depression) influence cognition via multiple possible paths. Meaning and purpose in life were associated with cognitive decline, and incident MCI and Alzheimer disease in prior studies [25]. In addition, studies investigating volunteering interventions to provide meaningful social, physical, and cognitive activities for older adults reduced brain aging [26]. RT is similarly organized to provide structured social engagement and stimulate cognitive activity through exercising autobiographical memory [27] and improvements in cognition may be mediated through improved life meaning and purpose. Depression is a well-known risk factor for cognitive decline [28] and loneliness and the relationship between loneliness and depression may be bidirectional [29]. In addition, apathy and depression are distinct neuropsychiatric conditions that often co-occur and symptoms may overlap [30]. Given the mechanisms of RT are not well understood, multiple aspects of social relationships and psychological well-being may be considered as mediators of the relationship between RT and health outcomes.

A growing body of research on RT for older adults targets individuals with ADRD and older adults in long-term care, as well as healthy older adults living in the community [18,20,21,31]. In addition, individual RT applied using virtual reality was shown to improve cognition and psychological well-being in institutionalized older adults, compared to traditional RT [32]. Studies on the effects of a virtually delivered group reminiscence therapy intervention that combines the benefits of a group intervention and is delivered virtually using communication technologies are scarce. The novelty of this proposal is that the intervention is designed, developed, and delivered via an established community-based organization by nonclinicians and has not been formally studied.

### Life Story Club

Life Story Club (LSC) is an established, nonprofit organization founded in Brooklyn, New York, in 2019. The organization is dedicated to reducing loneliness in older adults through RT and has already successfully served more than 1500 older adults. LSCs are virtual, no-cost RT clubs that meet weekly. The clubs are led by trained facilitators who propose 2 story prompts per meeting to invite participants to share their stories (eg, “As a child, what did you say you wanted to be when you grew up?” Or, “Tell a story about a time you or your loved one didn’t accept defeat.”). Participants alternate responding to prompts and sharing their stories. Facilitators are nonclinicians with teaching, arts, or social science backgrounds. Facilitators undergo comprehensive training including shadowing, on-the-job learning, and certification in Mental Health First Aid and SAFECare LGBTQ+ (lesbian, gay, bisexual, transgender, queer/questioning, and others) Cultural Competency Training prior to leading a club. LSC serves roughly 400 older adults per year and clubs are offered in English, Spanish, Mandarin, or Cantonese. In addition, groups can be phone or video-based to provide for broader access. Clubs can also be tailored based on particular interests such as LGBTQ+ clubs or cooking clubs.

Weekly sessions follow a structured format to ensure consistency and engagement. Weekly prompts are sent to participants via email, text, or phone 1-2 days before the meeting. Sessions begin with greetings and icebreakers. The facilitator then introduces the prompt and shares an example story. Each participant shares a 5-minute story related to one of the prompts and participants are encouraged to engage with the storyteller’s experience. Sessions conclude with final thoughts. LSC prompts are drawn from a library designed to evoke a range of autobiographical memories and reflections. Each week, prompts rotate across categories for broad depth and variety in storytelling experiences. LSC structure and prompt categories are detailed in Table 1.

**Table 1 table1:** Life Story Club program structure.

Parameters		Descriptions
**Weekly schedule**		
	Weeks 1-2	Introductory sessions with get-to-know-you prompts.
	Weeks 3-7	Sessions tailored to participants’ interests; participants take turns sharing stories based on weekly prompts.
	Week 8	Dedicated recording session where stories are recorded for archival purposes.
	Weeks 9-11	Regular storytelling sessions continue.
	Week 12	Special event for unveiling of the group’s Life Story Library.
**Prompt categories and examples**		
	Cultural and historical memories	What is a historical “first” you’ve lived through?
	Occasion-based memories	Can you tell us about a memorable celebration or gathering?
	Location-based memories	Tell us about a meaningful or memorable hangout spot in your life.
	Youth and childhood	Who was your childhood best friend?
	Career-based memories	Can you tell us about an extraordinary day at work?
	Current and future life	Can you share a story about a recent triumph?
	Relationships	What was something passed down to you from a family member, friend, or mentor?
	Identity and self-reflection	When was a time you changed your mindset or way of thinking?

Individuals are referred to LSC via primary care providers and through community outreach via naturally occurring retirement communities, public libraries, and older adult centers. Caregivers, family members, or individuals can also self-refer via the LSC website. RT as delivered by LSC can potentially improve accessibility and equity given its virtual delivery in multiple languages and can extend the reach of the intervention to homebound and rural older adults—the population who are at the highest risk for cognitive decline, tend to be hard to reach, and often not included in research for those reasons. LSC is a well-established community-based organization with a formalized infrastructure to serve community-based older adults.

### Study Objectives

The purpose of this study will be to explore the feasibility of a virtual group reminiscence therapy (vGRT) intervention delivered by LSC to improve loneliness and apathy in community-dwelling older adults. Rather than developing a new intervention, we propose to capitalize on an existing community-based resource to deliver a novel, virtual RT intervention directly to individuals in the community. We hypothesize that a virtual, group RT intervention will be feasible and acceptable for community-dwelling older adults.

## Methods

### Study Design

This study is a prospective, nonrandomized, mixed methods feasibility study testing the impact of the LSC intervention. The purpose of the proposed study design is to test the feasibility of the intervention and provide preliminary data for a larger randomized controlled trial (RCT).

### Recruitment

Participants will be recruited via partnerships with local community-based organizations serving older adults, home care agencies, as well as referrals from health care teams within the health system (eg, post-acute care managers, primary care social workers, and providers). Retention will be maximized by using preintervention counseling, regular opportunities for questions and feedback from participants, and compensation for completing pretest assessments, posttest assessments, and qualitative interviews at costs consistent with Institutional Review Board guidelines. All participants who participated in the LSC intervention will be invited to participate in qualitative interviews and we will enroll up to 30 participants or until saturation is reached.

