#### Intervention

LSC is a virtual, social storytelling space for older adults aged 60 and older where members can share life stories and connect with other members to promote a sense of belonging, purpose, and meaning. Clubs include up to 15 members that meet once a week for 1 hour. The number of participants per group is determined based on past levels of participation where 10-15 individuals are recruited per group and 6-8 attend each session due to the nature of the population (eg, multimorbidity and acute illness). The protocol for the study will not deviate from routine LSC protocols and will be offered similarly to the usual schedule and prompts as described in the introduction except for dedicated recording sessions which will be replaced by a usual session (Table 1). Clubs are led by a nonclinician facilitator who offers prompts to trigger discussion and reminiscence. Sessions begin with greetings after which 2 prompts are offered by the facilitator. The facilitator manages the group to encourage participation by all members. To promote technology equity (colloquially referred to as “techquity”), LSC has been delivered via live video or telephone according to participant preference to promote technology inclusiveness. Participants for this study will have the option to use video or telephone based on preference. The primary endpoint for this study will be 3 months based on durations of other RT interventions [31,34]. We will additionally collect assessment data at 6 months to preliminarily determine the feasibility and efficacy of a 6-month intervention in participants who continue to participate in the intervention over a longer period. Fidelity will be assessed via periods of observation by research staff to observe if components of the intervention are met (eg, 2 prompts per session and individual participation).

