### Data Collection

Assessments will be collected via telephone at baseline, 3 months, and 6 months post RT. Participants will receive a gift card for each completed assessment. Qualitative interviews will be conducted with a subset of 30 participants to assess satisfaction with the intervention, what aspects can be improved, and explore barriers and facilitators of participation, including digital literacy. A semistructured interview guide is included in Multimedia Appendix 1. Interviews will take place at an agreed-upon location over 60 minutes and will be conducted by the primary investigator or coinvestigator. We will collect data on the following outcome measures and covariates:

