#### Feasibility Outcomes

Feasibility will be determined by screening, enrollment, and acceptability of the intervention. Acceptability of the intervention will also be assessed via program satisfaction surveys (eg, satisfaction, mood, belonging, connection with members) at 3 months and 6 months as well as qualitative interviews to explore program acceptability, barriers and facilitators of participation, and technology accessibility. Outcome measures including feasibility and health outcomes are detailed in Textbox 1 and Table 2. Benchmarks are determined by prior LSC metrics and expectations for recruitment, enrollment, and participation based on prior LSC participants. The metrics we propose are based on study-specific retention efforts (eg, preintervention counseling, relationship building with participants, and participant incentives).

Feasibility outcomes.

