**Benchmarks**
No. of individuals screened/total referred (≥70% good)No. of individuals who agree/total screened (≥70 good)No. of individuals who complete 9/12 visits/total enrolled (≥70 good)SurveyOpen-ended interviewOpen-ended interview

**Table 2 table2:** Outcome measures.

Outcome measures			Assessment		Metrics

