### Data Analysis

The primary purpose of this exploratory project is to test the feasibility of an LSC intervention and to provide estimates of the efficacy of the LSC intervention to inform a future RCT. We will enroll a total sample size of 50 participants and expect an estimated 15% dropout rate. This sample size follows guidelines for pilot studies and is appropriate for exploring feasibility [51]. Descriptive statistics will be used to report sample characteristics, feasibility markers, and measures. Statistical analyses will be conducted using Stata (version 18.5; StataCorp LLC). Repeated-measures ANOVA will be applied to test for overall differences in loneliness and apathy at baseline, 3 months, and 6 months. Secondary outcomes will be analyzed for differences in trends before and after the intervention and associations with changes in loneliness and apathy. We will test whether these measures mediate changes in loneliness and apathy from baseline using linear regression models.

We will use field notes and memos throughout the qualitative interview process to explore qualitative data. Data will be deductively analyzed using NVivo 15 software.

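### The interview invitation leaves out enrolled people who never attend a session, and nothing ensures that early leavers are heard, although the interviews are the listed measure of barriers and technology access

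*Protocol article*

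**What the plan says.** The invitation rule stands in Methods, Recruitment: "All participants who participated in the LSC intervention will be invited to participate in qualitative interviews". The sentence goes on to the number: "we will enroll up to 30 participants or until saturation is reached". The article sets no minimum number of sessions for having participated and no rule for choosing among those who accept.

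Data Collection describes the same interviews without an attendance condition: "Qualitative interviews will be conducted with a subset of 30 participants to assess satisfaction with the intervention". It also gives them the task to "explore barriers and facilitators of participation, including digital literacy". Feasibility Outcomes repeats this, with "qualitative interviews to explore program acceptability, barriers and facilitators of participation, and technology accessibility". In Textbox 1, the open-ended interview is the entry against both barriers and facilitators and technology access.

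The quantitative acceptability benchmark in Textbox 1 uses a wider population: "No. of individuals who complete 9/12 visits/total enrolled (≥70 good". Data Analysis gives the sample: "We will enroll a total sample size of 50 participants and expect an estimated 15% dropout rate".

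**The concern.** The interviews are meant to explain why people do or do not take part, but the invitation depends on having taken part. A person who consented and then never joined a session may know most about access, digital literacy or lack of interest as reasons for not starting. The stated rule does not reach that person.

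The two strands of the mixed-methods design also cover different populations. The acceptability benchmark counts a never-attender in the denominator and as a failure. The interviews have no route to the reason. If acceptability falls short of 70%, the qualitative strand cannot say why some people never started, which a pilot for a larger randomised trial needs to know.

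A second, weaker gap concerns people who start and then leave. They may be interviewed, but the places can be filled, or saturation declared, without any of them. Saturation among regular attenders does not show that the reasons for leaving have been exhausted.

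**Working it through.** The plan derives no figure for the composition of the interview sample, so there is none to reproduce. The check compares the populations and then uses the plan's own counts.

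**Inputs.** Enrolled N = 50 and dropout 15% (Data Analysis); benchmark 70% completing 9 of 12 sessions (Textbox 1); at most 30 interviews (Recruitment).

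**Step 1: who is in each frame.**

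| Group among the 50 enrolled | Invited to interview as written | In the acceptability benchmark |
|---|---|---|
| Completed at least 9 of 12 | Yes | Yes, success |
| Attended some, fewer than 9 (includes early leavers) | Yes, no minimum is set | Yes, failure |
| Attended none | No | Yes, failure |

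Only the last row is excluded by rule. Its size cannot be derived from the document.

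**Step 2: can completers fill every place?** Completers at the benchmark: 0.70 × 50 = 35. Non-completers: 50 − 35 = 15. Since 35 > 30, they can. It would take acceptance by 30/35 = 86% of completers, or less if saturation is declared before 30. By the dropout figure, 0.15 × 50 = 7.5 leave and 42.5 stay; those who stay could fill the places at 30/42.5 = 71% acceptance.

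**Step 3: is such a sample likely?** The text allows it but does not force it. Suppose 30 of the 50 were drawn at random, every leaver had attended at least once, and all accepted. The expected number of leavers interviewed is 30 × k/50:
- k = 7: 4.2, with a chance of none of 0.08% (hypergeometric)
- k = 8: 4.8, with a chance of none of 0.02%
- k = 15 (all non-completers): 9.0, with a negligible chance of none

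The plan states neither random selection nor equal acceptance.

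**Step 4: unequal acceptance (assumed rates).** Take 80% among completers, giving 0.80 × 35 = 28 willing.
- Non-completers at 40%: 0.40 × 15 = 6 willing; share of 30 places = 30 × 6/34 = 5.3
- Non-completers at 30%: 0.30 × 15 = 4.5 willing; share = 30 × 4.5/32.5 = 4.2

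So about 4 to 5 of 30 would be non-completers, against 9 under proportionate sampling. Some non-completers may be never-attenders, who contribute 0 under the stated rule, so these counts are upper values for the assumed rates.

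**The case against.** A reader might infer that early leavers are shut out and that barriers are described only by people who overcame them. The text does not support that. Participation carries no threshold, so someone who came once and left is invited, and Step 4 itself puts several non-completers among the interviewees.

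A reader might also take the interviews to be the only source on these questions, and acceptability to be biased upwards as a result. That goes too far. The Discussion plans quantitative as well as qualitative data on technology access. Acceptability is also measured by attendance over all enrolled, which already counts never-attenders against the programme, and by satisfaction surveys. What none of these is stated to provide is the reasons for never starting.

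The Intervention section's "10-15 individuals are recruited per group and 6-8 attend each session" gives 6/15 = 40% to 8/10 = 80%. That is past attendance per session, linked there to illness in this population. It is not a rate of never starting or of dropping out, and people who miss some sessions stay eligible. Feasibility Outcomes also expects study-specific retention efforts to help. Excluding people with neither internet nor telephone, and offering telephone participation, plausibly reduces failure to start for technical reasons.

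The condition appears in one sentence and may be loose wording for everyone enrolled, since Data Collection speaks only of a subset of participants. How interviewees are chosen from those invited, and how saturation is judged, can fairly be left to a full protocol that is not shown. This argument stands against faulting the article for lacking quotas. It does not answer the invitation rule itself, which the article states and which, read literally, leaves out the never-attenders.

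**Conclusion.** The point holds in a limited form. As written, enrolled people who attend no session are outside the interview frame, while the same interviews are the listed measure of barriers to participation and of technology access. Early leavers are inside the frame, but their presence is left to chance: at the 70% benchmark, the 35 completers could supply all 30 interviews.

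The number of never-attenders is unknown, so the loss cannot be sized for the only group excluded by rule. The figure of 4 to 5 non-completers in 30 rests on assumed acceptance rates and shows direction only. The loneliness and apathy analyses and the quantitative benchmarks are unaffected. This is a cheap improvement to a stated feasibility aim.

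**What to change.** Replace the invitation sentence in Recruitment with: *All enrolled participants, including those who never attended or who withdrew, will be invited to a qualitative interview.* Keep the maximum of 30. Invite people when they stop attending, or when it is clear that they have not started, because reasons are harder to recover later. State the aim of purposively including non-attenders and people below 9 of 12 sessions. Report the attendance of interviewees beside that of all 50 enrolled, so that readers can see whom the findings represent.

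Do not set a fixed quota. Reserving 8 to 10 places for the 15 non-completers would need 8/15 = 53% to 10/15 = 67% of them to accept. At the assumed 30% to 40%, only 4.5 to 6 would, which is also too few to judge saturation separately.

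The cost is a wording change, best made before recruitment (planned for July 2025), and earlier invitations for some people. The maximum number of interviews and the interviewers stay the same, and oral consent before interview is already planned. The small downside is that non-attenders are harder to recruit, and the document does not say how many there will be.
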